### Study 3: Development of the ESM Survey

This study aims (1) to identify a relevant and suitable clinical behavior and (2) to develop an ESM survey to assess this target behavior in routine clinical care. The survey will be part of our standard diagnostic procedure, allowing patients and psychotherapists to add individualized items if desired. The survey's specific content is less critical for implementing the SCED infrastructure and can be replaced or expanded in future research studies based on other variables of interest. However, it is a significant gap in SCED infrastructure implementation that validated ESM surveys are still limited (for a positive example see https://esmitemrepositoryinfo.com/). It is needed if it should be possible to aggregate the generated SCED data across patients (e.g., to investigate overarching research questions). We plan to follow recommendations in questionnaire development and validation, following sequential phases of item generation, scale development and scale validation (Boateng et al., 2018). During this process, a minimum of six stakeholders each will be consulted at several stages until information saturation is reached (for a justification of the sample size see Study 1). For example, patients will be involved via cognitive interviews to ensure the comprehensibility of the items (Darnall et al., 2017). Psychotherapists will be involved to ensure that the m-path data dashboard is used in a meaningful way for clinicians (Guest et al., 2006). Besides content validity, it will be crucial to assess its suitability as a SCED instrument, e.g. in terms of sensitivity to intrapersonal change (Lavefjord et al., 2021), and to consider the potential non-stationarity of the data (Ryan et al., 2023).

We propose to apply a twofold assessment strategy which yields the potential to understand the individual’s model in reference to what is normative (Wright & Zimmermann, 2019) and to capture complex change processes that are of greatest relevance to individual clients being also most consistent with the clinical reality of psychotherapeutic work (Lloyd et al., 2019).

#### Emotion Regulation

As a first draft of an ESM survey, we decided to focus on emotion regulation as an important transdiagnostic mechanism to complement the thus far primarily symptom-oriented diagnostics with a mechanistically informed approach. Emotion regulation refers to the ‘ability to modulate the intensity, frequency, and duration of positive and/or negative emotions’ (Boemo et al., 2022, p. 1). It is a dynamic, multi-stage process (Gross, 2015), making it well-suited for ESM measurement. Emotion regulation is crucial in psychological disorder development and maintenance (Fernandez et al., 2016). Understanding its complexity in everyday life can reveal regulation difficulties and inform targeted therapeutic interventions (Aldao et al., 2015; Gross & Jazaieri, 2014). Moreover, emotion regulation could be studied more rigorously as mechanism of change in psychotherapy (Palmieri et al., 2022). We plan to include the following emotion regulation processes in the ESM survey: momentary affect (Cloos et al., 2022), information on the appraisal of specific situational contexts (Doré et al., 2016), emotion regulation strategies (Boemo et al., 2022), emotion regulation motives (Tamir, 2016), and emotion regulation success (Gruber et al., 2012). This would allow a differentiated assessment of an important transdiagnostic mechanism within and across patients. Data provides important insight for psychotherapy independent from specific diagnosis and could still be aggregated across patients.

#### Idiographic Items

Above that, two idiographic items are formulated, a problem-focused and goal-focused idiographic measure. Idiographic measures offer personalized insights and empower clients (Elliott et al., 2016; Wright & Zimmermann, 2019). Especially, goal-setting has been shown to have effects of *d* = 0.34-0.40 of its own (Epton et al., 2017; Harkin et al., 2016). However, the item generation is not without challenges (Sales et al., 2023). The identification of relevant problems and goals is a difficult task as patients might not always be able to report their problems and goals in clear and precise manners. Also, problems and goals might change throughout the process of psychotherapy. For those reasons, we plan to build upon existing measures. According to two recent systematic reviews (Lloyd et al., 2019; Sales & Alves, 2016) examples for short problem-focused measures that could serve as a starting point are the Simplified Personal Questionnaire (PQ; Elliott et al., 2016; Shapiro, 1961) and the Psychological Outcome Profiles (PSYCHLOPS; Ashworth et al., 2005) and goal-focused measures are Goal Attainment Scaling (Kiresuk & Sherman, 1968), Goals Form (Cooper & Xu, 2023), and Youth TOP Problems (Weisz et al., 2011).

### Study 4: Testing Usability and Feasibility

In the *optimization phase*, the aim is to test usability and feasibility and to customize the SCED infrastructure accordingly. We plan to carry out several SCED iterations using a replicated ABC(DE) design (see Table 1; Tate et al., 2013). Each iteration will comprise 6–12 patient-therapist dyads (Bartels et al., 2022). To accelerate the optimization process, only phases A, B, and C are initially included to identify critical points of improvement. Phases D and E will be carried out, but they will not be decisive for the optimization process. Based on the draft of the ESM protocol, the respective phases should comprise 14 assessment days. Patient-therapist dyads are informed that participation also includes a subsequent stakeholder meeting. The results of each iteration will be presented at the respective stakeholder meeting. Stakeholders will collaboratively identify areas for improvement in each component of the infrastructure. Based on this, they may choose to initiate further rounds of iterations. The optimization loop continues until stakeholders agree that the infrastructure is ready for the implementation phase. Decisions will be consensus-based, requiring agreement from all stakeholders. Figure 3 presents an overview about the design and process of the optimization phase.

**Fig. 3 Fig3:**
[figure not shown]
Design and process of the optimization phase

#### Usability Measures

A mixed methods approach will be used to determine the usability of the SCED infrastructure, including questionnaires, technical data, and semi-structured interviews (see Table 2). Questionnaires will be administered at the end of each SCED phase with the concluding assessment comprising questionnaires and a semi-structural interview 6 weeks after the intervention started. To facilitate its evaluation, we decomposed the infrastructure into the following components: initial expectations, the onboarding process, the practical use of the m-path app, the feasibility of the ESM protocol and survey (including possible negative side effects), the clarity of the visual dashboard, the utility for clinical practice, and data management aspects.

**Table 2 Tab2:** Usability Measures (Study 4)

Questionnaires	ESM data	Semi-structural interview
• Adapted System Usability Scale (SUS) (Brooke, 1996; Lyon et al., 2020) to evaluate the usability of the m-path app (e.g., *‘I think I would like to use this app frequently.’*) and dashboard with the visual presentation of the ESM data (e.g., *‘I think I would like to use this dashboard frequently.*’) on a 5-point Likert Scale (1 = strongly disagree to 5 = strongly agree) • User Experience Questionnaire (UEQ-S) (Schrepp et al., 2017) to assess the subjective impression of users towards the user experience of the m-path app on a 7-point Likert scale (-3 = fully agree with negative term) to + 3 = fully agree with positive term) grouped into 6 subscales: *attractiveness, perspicuity, efficiency, dependability, stimulation, novelty*	• Patients have to rate of how burdensome (0 = neutral to 10 = disturbing) and helpful (0 = neutral to 10 = helpful) each survey is *(‘How do you rate the survey today?*’) • Response times, compliance rates, and indicators of careless responding will be retrieved from the ESM surveys • ESM data will be merged with data routinely collected at the outpatient clinic (such as clinical diagnosis, severity of symptoms, and sociodemographic data); difficulties emerging during this process will be recorded in a protocol to be able to resolve the issues for future iterations	Interview questions are intended to cover different components of the SCED infrastructure: • Initial expectations (e.g., *‘What did you expect at the beginning? Have these expectations been met?’*) • Onboarding process (e.g., *‘How can we improve the onboarding process?’*) • Practical use of the m-path app (e.g., *‘How did you get on with the m-path app?’*) • Feasibility of the ESM protocol and survey (e.g., *‘Would you change anything about the survey, including the frequency of assessment?’*) • Negative side effects (e.g., *‘Did you experience any negative side effects? How could negative side effects be reduced?’*) • Clarity of the dashboard (e.g., *‘Did you use the dashboard? What would you like to change about the dashboard?*’) • Utility for clinical practice (e.g., *‘Was the app part of the treatment/supervision? What could be changed to maximize its utility?’*)

Note. Usability measures will be administered to both patients and psychotherapists after each SCED phase; supervisors will also be invited to rate the System Usability Scale (SUS) to evaluate the dashboard (i.e., the visual presentation of the data) and conduct the semi-structural interview

#### Feasibility Measures

Feasibility is evaluated along the outcome domains of implementation research that are commonly used in feasibility studies (Arain et al., 2010; Proctor et al., 2011): *Acceptability* and *appropriateness* are assessed as part of the usability measures. Feasible *adoption* is reflected in participation (≥ 50% offered using the SCED infrastructure will enroll in the study and ≥ 70% of the participants who enrolled will complete participation; Frumkin et al., 2021). Reasons for drop-out will be assessed if participants consent to provide information. In addition, *penetration, compliance* and *retention* will be monitored.

### Study 5: Piloting the Implementation of the SCED Infrastructure

The study aims (1) to determine how users accept, perceive, adopt, and integrate the SCED infrastructure into routine clinical care and (2) to use results to initiate strategies for further improvement. For that reason, the SCED infrastructure will be offered in routine clinical care to generate first evidence regarding perceptual and behavioral implementation domains. We intend to offer all new admissions to our clinic to use the SCED infrastructure for a 1-year period. Both patients (irrespective of their clinical diagnosis except for acute suicidal tendencies and psychotic symptoms) and psychotherapists will be invited to participate in the implementation study. We expect to have approximately 250 new admissions in a 1-year period. On average, during the last five years we had 295 new admissions per year, but due to the change of the system we expect a slight decrease. In 2021 and 2022, we had 77 active psychotherapists and 72 respectively. The number of patients and psychotherapists who decide to use the infrastructure will be used to estimate the adoption rate as one implementation outcome (see Section “Implementation Outcome Measures” and Table 3 for more information).

**Table 3 Tab3:** Implementation Outcome Domains and Measures (Study 5)

Domain	Definition	Concrete Operationalization	Measure	Criteria
Acceptability and Appropriateness	Acceptability is defined as the perception among different stakeholders that an innovation is agreeable, palatable, or satisfactory Appropriateness refers to the perceived fit, relevance, or compatibility of an innovation for a given practice or setting	Degree that patients and psychotherapists think the SCED infrastructure is acceptable and helpful to improve clinical practice in an outpatient setting	(1) The tool (i.e., the handling of the m-path app) and dashboard (i.e., the visual presentation of the data) are rated independently on a 5-point Likert scale (1 = ‘strongly disagree’ to 5 = ‘strongly agree’): • *‘The tool is acceptable for clinical practice’* • ‘*The tool is helpful for clinical practice’* • *‘The dashboard is acceptable for clinical practice’* • ‘*The dashboard is helpful for clinical practice’* (2) Three subscales of an adapted version of the Adoption of Information Technology Innovation Measure (Moore & Benbasat, 1991) are rated on a 7-point Likert Scale (1 = ‘extremely disagree’ to 7 = ‘extremely agree’): • Relative advantages (e.g., *‘Using the tool improves the quality of the treatment’*), • Compatibility (e.g., *‘Using the tool is completely compatible with my current situation’*) • Ease of use (e.g., *‘Overall, I believe that the tool is easy to use’*) (3) Adapted version of the Evidence-based Practice Attitudes Scale (EBPAS; Aarons, 2004) together with its extension (Aarons et al., 2012)	(1) Mean scores of > 3.5/5 on each item are considered sufficiently acceptable and appropriate (2) Mean scores of > 4.5/7 on each subscale are considered sufficiently advantageous, compatible, and easy to use (3) N/A
Adoption	Adoption comprises the intention, intentional decision, or action to try or employ an innovation	Number of individuals who are willing to use the SCED infrastructure (i.e., who consent to test the infrastructure as part of the study)	(4) Number of patients and psychotherapists who decided to use the infrastructure divided by the number of invitations (i.e., new admissions to the clinic)	(4) A rate ≥ 50% is considered substantial demand
Penetration	Penetration refers to the integration of a practice within a setting	Number of patients and psychotherapists who actually use the SCED infrastructure (e.g., in terms of responding to the ESM surveys; retrieving and discussing the dashboard during treatment or supervision)	(5) ESM data (including signal- and event-contingent surveys of completed ESM surveys (i.e., the last question has been answered)) is used to derive an estimate for the penetration: • Exploration of arithmetic values (e.g., median, range, mean standard deviation) for the number of completed ESM surveys for each SCED phase, especially for the open-ended intervention phase • RoBiNT scale requires each phase to consist of at least five, but not less than three data points for the analysis of SCED data (Tate et al., 2013). We will evaluate each phase separately, with ≥ 5 data points as an acceptable criterion. For each phase, we divide the number of patients who fulfill the acceptable (≥ 5 data points) criterion by the number of participating patients (6) Indication how often patients and psychotherapists retrieved the dashboards either to prepare for treatment or discuss the dashboard during treatment on a 5-point Likert scale (1 = never to 5 = every session) after each SCED phase. Psychotherapists will also be asked to indicate how often they discussed the dashboard with their supervisors • *‘How often did you retrieve the dashboard (e.g., to prepare for treatment or discuss the dashboard during treatment)?’* • *‘How often did you discuss the dashboard together with your supervisor?’*	(5) A rate ≥ 75 is considered substantial use (6) Mean scores of > 3.5/5 on each item are considered substantial use
Implementation costs	All costs needed for an implementation effort	All monetary resources needed for the implementation of the SCED infrastructure. These costs could either be anticipated (e.g., for the m-path software) or unexpected (i.e., they only become clear in the course of implementation)	Implementation costs are also difficult to calculate because they vary substantially in the different settings (7) A list of the costs we have incurred (e.g., required working time of an employee to coordinate the single-case clinic)	
Compliance and Retention Rates	Compliance refers to the ratio of completed surveys over the theoretical maximum number of surveys Retention refers to the proportion of participants included in the final analyses	Compliance and retention rates to the ESM surveys intend to evaluate to what extent the data generated in a routine clinical setting could be used for future data analyses to address overarching research questions	(8) Ratio of completed signal-contingent surveys divided by the number of theoretically possible surveys (as an indicator for compliance) (9) Proportion of participants who responded to at least five of the signal-contingent surveys after data cleaning (as an indicator for retention)	(7) Rates of 70–80% are considered satisfactory compliance (8) Rates of 90% are considered satisfactory retention

Note. Definitions are derived by Proctor et al. (2011). Implementation outcome measures will be administered to both patients and psychotherapists after each SCED phase; only the Evidence-based Practice Attitudes Scale (EBPAS) will be administered once at the study beginning (i.e., when patients and psychotherapists decide whether to use the SCED infrastructure); this will allow to compare individuals who are willing to use the SCED infrastructure with those who are not. Criteria for a successful implementation were chosen according to previous research (Schleider et al., 2020); criteria for compliance and retention rates were formulated based on systematic reviews (Rintala et al., 2019; Vachon et al., 2019; Wrzus & Neubauer, 2023); it should be noted, however, that these values were estimated in the context of research studies (as opposed to a routine clinical care setting)

To evaluate our implementation process, we assess several perceptual and behavioral outcome domains (Proctor et al., 2011). We hope to obtain some outcome measures from people who are willing to use the SCED infrastructure, as well as those who are not interested. This will allow us to conduct some exploratory analyzes about how these groups differ. For patients, we expect to collect a relatively diverse sample which will probably allow such a comparison.

Results of the initial implementation study will be a first indicator for the expected sustainability of the SCED infrastructure in our clinic. In case, results do not meet our predefined criteria for a successful implementation, the research team will develop a proposal for another implementation strategy plan (Kirchner et al., 2020b; Powell et al., 2015) to maintain and further improve the uptake of the SCED infrastructure. Other implementation strategies could comprise the provision of interactive assistance or the training of stakeholders. Again, the implementation plan will be optimized and finalized together with different stakeholders. In either case, we plan to replicate the pilot implementation study for another year, with the goal to either test whether implementation outcomes substantially improve compared to the first implementation round or to evaluate its sustainability.

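### The Study 5 adoption rate counts psychotherapists in the numerator but divides by patient admissions only, so the ≥ 50% criterion can be met when true adoption is 38–39%

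*Protocol article*

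**What the plan says.** Table 3 (Study 5), Adoption, measure (4), sets the rate as "Number of patients and psychotherapists who decided to use the infrastructure divided by the number of invitations (i.e., new admissions to the clinic"). The criterion in the same row is "A rate ≥ 50% is considered substantial demand".

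The Study 5 text supplies the quantities. On admissions: "We expect to have approximately 250 new admissions in a 1-year period", against a history in which "On average, during the last five years we had 295 new admissions per year". On staff: "In 2021 and 2022, we had 77 active psychotherapists and 72 respectively". It also states that patients "and psychotherapists will be invited to participate in the implementation study", so invitations go to both groups. It describes one combined measure: "The number of patients and psychotherapists who decide to use the infrastructure will be used to estimate the adoption rate as one implementation outcome".

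Later in the Study 5 section, failure to meet the predefined criteria leads the research team to propose another implementation strategy plan. The pilot is then repeated for a further year in either case, to see whether outcomes improve or are sustained.

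**The concern.** Numerator and denominator refer to different populations. The row explains invitations as new admissions, and new admissions are patients. Psychotherapists who agree are added on top, while the invitations they received are left out. Nothing in the Study 5 section or the notes to Table 3 adds them to the denominator or sets a separate rate for each group.

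The article matches its denominators elsewhere. In Study 4, adoption is the share enrolling among those offered the infrastructure. In Table 3, measure (5), patients with enough data points are divided by participating patients.

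Two uses of the rate are at stake. First, it is one of the criteria that decide whether the implementation strategy is revised, and an inflated value could show substantial demand when most patients decline. Second, the planned second year invites a comparison between years, and the printed rate moves with the ratio of psychotherapists to admissions even if nobody's behaviour changes.

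**Working it through.** The article states a threshold but no expected adoption figure, so there is no printed result to reproduce. The check applies the rule to the article's own numbers.

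**Inputs**
- A = 250 expected new admissions (Study 5 text); 295 as a sensitivity value (five-year average, same paragraph).
- T = 72 or 77 active psychotherapists (Study 5 text).
- Criterion 50% (Table 3, measure 4).
- f = share of psychotherapists who adopt. The article gives no value, so it is an assumption, varied from 0 to 100%.

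**Rule as printed:** (adopting patients + adopting psychotherapists) / A. At A = 250 the criterion needs 0.5 × 250 = 125 adopters.

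**1. Ceiling.** (A + T)/A = 322/250 = 128.8% for T = 72, and 327/250 = 130.8% for T = 77. The same factor, 1.288 to 1.308, is the inflation over a combined rate whose denominator counts everyone invited.

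**2. Equal uptake p in both groups.** The rule passes when p(A + T) ≥ 125. That is p ≥ 125/322 = 38.8% (T = 72) or 125/327 = 38.2% (T = 77).

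**3. Unequal uptake.** Patients needed = 125 − f × T, with f × T rounded to whole persons.

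| Psychotherapists adopting | Patients needed, T = 72 | Patients needed, T = 77 |
|---|---|---|
| 0% | 125 (50.0%) | 125 (50.0%) |
| 25% | 107 (42.8%) | 106 (42.4%) |
| 50% | 89 (35.6%) | 87 (34.8%) |
| 75% | 71 (28.4%) | 67 (26.8%) |
| 100% | 53 (21.2%) | 48 (19.2%) |

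The first row shows the reverse problem: 125 patients and no psychotherapist also pass. The rate therefore guarantees nothing about psychotherapist uptake.

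**4. Sensitivity to admissions.** With A = 295 the criterion needs 148 adopters (147.5 rounded up). If all psychotherapists adopt, 76 patients (25.8%, T = 72) or 71 (24.1%, T = 77) are enough.

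**5. Drift with constant behaviour.** Assume that 40% of patients and 60% of 75 psychotherapists (45) adopt. At 295 admissions the rule gives (118 + 45)/295 = 55.3%. At 250 it gives (100 + 45)/250 = 58.0%. Both pass although only 40% of patients adopt, and the rise of 2.7 points comes only from the fall in admissions.

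**6. Would a corrected combined rate do?** With denominator 322 or 327 the criterion needs 161 or 164 adopters. If all psychotherapists adopt, 161 − 72 = 89 patients (35.6%) or 164 − 77 = 87 (34.8%) would still pass. Only separate rates ensure that a pass means at least half of the patients.

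**The case against.** The strongest counter-argument is that the row may be meant per case: one invitation per admission, counted as adopted when patient and psychotherapist both agree. The denominator would then fit and the ratio could not exceed 100%. Study 4 is organised by patient-therapist dyads, which lends this some support. However, the Study 5 text and Table 3 speak of the number of patients and psychotherapists who decide to use the infrastructure, and do not mention agreement within a dyad. Other lenient readings fail too. Separate rates over admissions would cap psychotherapists at 77/250 = 30.8%, so they could never meet 50%. Counting a psychotherapist once per admission would raise the ceiling to 200%. What stands is that the sponsor may have intended something coherent; the printed rule does not say so.

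Three stronger conclusions are tempting, and the documents do not support them:
- A reader might infer that about 20% patient uptake is typically enough. That needs every active psychotherapist to adopt while about four in five patients decline. It is the extreme of the range.
- A reader might use the 98 therapists of the Setting section (80 in training plus 18 licensed), which would lower the patient share needed still further. Study 5 gives its own count of active psychotherapists, 72 to 77, and that is the relevant figure.
- A reader might object that the denominator also includes admissions who are not eligible, since patients are invited "irrespective of their clinical diagnosis except for acute suicidal tendencies and psychotic symptoms". That follows only if the explanation in brackets overrides the word invitations. It would also push the rate down rather than up, and no number is given.

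Two further points hold. The consequence is limited: adoption is one of several criteria, the pilot is repeated whatever the result, and no hypothesis test or sample size rests on this rate. Also, the article attributes its implementation criteria to earlier research that is not available here, so the unit to which 50% was meant to apply cannot be confirmed.

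**Conclusion.** The concern holds as an error in the definition of an outcome. Followed as printed, measure (4) is not a proportion and overstates adoption among those invited by a factor of 1.29 to 1.31. Equal uptake of 38–39% in both groups meets a criterion labelled 50%. Patient uptake of about 35% is enough if half of the psychotherapists adopt, and 19–21% if all do.

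These figures rest on 250 admissions, on 72 to 77 psychotherapists each counted once, and on an assumed psychotherapist uptake. The direction of the bias does not depend on the last: any adopting psychotherapist lowers the number of patients needed.

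The correction should be made, because the rate feeds the decision on a new strategy and the comparison between years. It is not a flaw that undermines Study 5 as a whole, since both counts have to be collected to compute the printed rate and the separate rates can be recovered from them.

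**What to change.** Replace measure (4) in Table 3 by two rates with matched denominators:
- consenting patients divided by patients invited;
- consenting psychotherapists divided by psychotherapists invited, each person counted once.

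Judge each against the stated 50%. With the expected numbers this means at least 125 of 250 patients, and at least 36 of 72 or 39 of 77 psychotherapists. If the sponsor intended the 50% for one group only, the row should say so. Bring the sentence on the adoption rate in the Study 5 text into line.

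The share of invited patients for whom patient and psychotherapist both agreed could be reported in addition; this is optional.

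The cost is the wording of one table row and one sentence, with no new data collection. The reported adoption figure will be less favourable than under the printed rule.

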### Setting

The SCED infrastructure will be implemented in the outpatient clinic of the RPTU Kaiserslautern-Landau in Germany. The outpatient clinic is part of a project for coordinating research efforts in German university outpatient clinics for psychotherapy that guides current standard diagnostic procedures (Velten et al., 2017). Standard diagnostic procedures comprise up to four diagnostic sessions and include an intake interview by a licensed psychotherapist, further clinical interviews and questionnaires. The Symptom Checklist 90 (SCL-90, Derogatis & Unger, 2010; Franke, 2014) together with symptom-specific questionnaires is administered at intake, during the diagnostic sessions, during treatment (every 10th session), at posttreatment and at 6-month follow-up.

Around 800 adults with mental disorders are treated per year. Eighty therapists in training and 18 licensed psychotherapists deliver about 45 treatments per day. In Germany, public health insurance usually covers short-term treatment of 24 sessions, which can be extended to up to 80 sessions in total, depending on the mental state of patients. In addition, therapies are implemented within the framework of third-party funded and self-funded psychotherapy studies. The treatment delivered is Cognitive Behavioral Therapy (CBT). The outpatient clinic is a facility that teaches bachelor's graduates who are pursuing their master's degree in psychotherapy and master's graduates who are training to become licensed psychotherapists with a special emphasis on CBT. Adherence to standard CBT methods is safeguarded by regular supervision. Bachelor graduates receive intensive one-on-one supervision by a licensed psychotherapist, who could directly intervene in the case of an emergency, while working with patients. Master graduates receive regular group and individual supervision by a licensed psychotherapist with more than five years of work experience.

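### Study 5 adoption rate: patients and psychotherapists are counted in the numerator, but the denominator is glossed as new admissions and leaves out the invited psychotherapists

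*Protocol article*

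**What the plan says.** Table 3 (Study 5), Adoption, measure (4), is a ratio: "Number of patients and psychotherapists who decided to use the infrastructure divided by the number of invitations (i.e., new admissions to the clinic"). The operationalization in the same row counts individuals, namely those "who consent to test the infrastructure as part of the study". The criterion is a single rate of at least 50%.

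The Study 5 text describes who is approached. New admissions over one year are to be offered the infrastructure, and about 250 are expected. Patients are invited to the study "irrespective of their clinical diagnosis except for acute suicidal tendencies and psychotic symptoms". Alongside them, "psychotherapists will be invited to participate in the implementation study". Their number is given separately: "In 2021 and 2022, we had 77 active psychotherapists and 72 respectively".

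Study 4 (Feasibility Measures) uses the same 50% threshold with a different base, those who received the offer: "50% offered using the SCED infrastructure will enroll in the study".

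If the predefined criteria are missed, the research team proposes another implementation strategy plan. In either case the pilot is repeated for a further year, "with the goal to either test whether implementation outcomes substantially improve compared to the first implementation round or to evaluate its sustainability".

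**The concern.** A proportion compared with a 50% threshold needs a numerator drawn from its denominator. Psychotherapists are not admissions to the clinic, yet those who adopt are added to the numerator while those invited do not enter the denominator. The ratio is then not a proportion, and 50% no longer means that half of those asked said yes. Because psychotherapists equal more than a quarter of the expected admissions, their uptake can carry the measure past the threshold while most patients decline. The result would be reported as substantial demand, and adoption would not be among the criteria that prompt a new strategy plan.

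There is a secondary question about the patients. If those excepted from the study invitation stay in the denominator, they count as non-adopters although they could not have consented.

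**Working it through.** The protocol states a threshold but no computed adoption figure, so there is nothing to reproduce first.

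**Inputs**
- Admissions A = 250 (expected, Study 5); sensitivity A = 295 (five-year average, Study 5).
- Psychotherapists T = 72 (2022) or 77 (2021), Study 5. The Setting section gives a larger staff ("Eighty therapists in training and 18 licensed psychotherapists deliver about 45 treatments per day"). I use the Study 5 counts; the larger figure would only widen the discrepancy under pooling.
- Each psychotherapist is counted once, following the operationalization by individuals.
- e = share of admissions not invited. The protocol does not give it. The main results use e = 0, and a range is shown at the end.

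**Pooled reading:** rate as written = (adopting patients + adopting psychotherapists) / A.

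| Quantity (A = 250, e = 0) | T = 72 | T = 77 |
|---|---|---|
| Maximum, (A + T)/A | 322/250 = 128.8% | 327/250 = 130.8% |
| Shown when true uptake is 50% in both groups | 161/250 = 64.4% | 163.5/250 = 65.4% |
| Patients needed to pass if all psychotherapists adopt, (125 − T)/A | 53/250 = 21.2% | 48/250 = 19.2% |
| Share of all invited that 125 adopters represent | 125/322 = 38.8% | 125/327 = 38.2% |

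Example in which the conclusion reverses (T = 72): 36 psychotherapists (50%) and 89 patients (35.6%) adopt. As written, 125/250 = 50.0%, a pass. Over everyone invited, 125/322 = 38.8%, a fail.

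With A = 295 the maximum is 367/295 = 124.4% (T = 72) or 372/295 = 126.1% (T = 77). Passing takes 148 adopters. If all psychotherapists adopt, 76/295 = 25.8% or 71/295 = 24.1% of patients is enough.

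**Separate reading, both rates over admissions:** the psychotherapist headcount rate is at most 72/250 = 28.8% or 77/250 = 30.8%, below 50% even with full uptake.

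**Secondary effect of excepted patients:** a true 50% uptake among invited patients shows as 0.50 × (1 − e), which is 47.5%, 45.0% or 40.0% for e = 5%, 10% or 20%. In the pooled ratio this works against the psychotherapist effect. With T = 72 and true uptake of 50% in both groups, the ratio shows 0.50 × (1 − e) + 36/250, which is 61.9%, 59.4% or 54.4%. The two effects cancel only at e = 72/250 = 28.8%.

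**The case against.** The strongest defence reads invitations per admission. Each new admission prompts one decision by the patient and one by the treating psychotherapist. The section on implementation outcome measures collects data from both when they decide, and Study 4 works with patient-therapist dyads. With two separate rates per admission, admissions would be the right base for both, and each would lie between 0 and 100%. The protocol also never says outright that the two groups are summed.

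This shows that the wording is open, and that the figures above depend on counting people once. It does not rescue the measure. The operationalization counts individuals, not decisions per admission, and the Study 5 text speaks of one adoption rate estimated from both groups. Two per-admission rates are stated nowhere. Pooling per-admission decisions instead would allow up to 200%.

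A second objection is that excepted patients may not be a real problem. Study 5 says that all new admissions are offered the infrastructure, and Table 1 (Replication) plans an offer to all patients and psychotherapists. A reader might infer that the denominator certainly includes people who were never invited, but the documents do not settle that. The exception attaches to the study invitation, it sits beside a statement that points the other way, and its size is not given. It remains a secondary point.

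Third, the two group counts must both be collected, so group-specific rates could be recovered later, and a ratio above 100% would be noticed. That is true, but a misleading value between 50% and 100% would not be noticed.

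**Conclusion.** The point holds for the psychotherapist mismatch, which follows from the text without any assumption about excepted patients. Counting individuals, with 250 admissions and 72 psychotherapists, the pooled ratio overstates a true 50% by 14.4 percentage points and can be passed with about one patient in five. If the rates are separated but both kept over admissions, the psychotherapist headcount cannot reach the threshold. These sizes rest on one count per psychotherapist and on the protocol's own expected numbers. The possible understatement of the patient rate is secondary and of unknown size.

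A reader might infer that 50% is unreachable for psychotherapists under any reading, or that an erroneous pass would end the evaluation. Neither is supported. The first depends on headcounts. As to the second, adoption is one of several descriptive criteria and the pilot is repeated in either case. What is affected is the reported adoption figure, whether a new strategy plan is triggered, and hence whether the second year tests improvement or sustainability.

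**What to change.** In Table 3, measure (4), delete the gloss that equates invitations with new admissions, and judge two rates separately against 50%:

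- consenting patients / patients invited;
- consenting psychotherapists / psychotherapists invited, each counted once.

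Report the number of admissions not invited. This also brings the measure into line with the base used in Study 4.

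The rates should not be pooled, even over the right denominator: with 322 invited, 161 adopters pass, and if all 72 psychotherapists adopt, 89/250 = 35.6% patient uptake is enough.

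The cost is one wording change and one tally kept at admission, with no extra patients or procedures.
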